#### Primary outcome

Muscle biopsies will be collected from m. vastus lateralis using the Bergstrom-technique [7]. The muscle samples are immediately mounted with Tissue-Tek and frozen in isopentane cooled with liquid nitrogen, and stored at -80°C until further investigation. The post intervention biopsy will be obtained at 1 cm either distally or proximally (randomized) to the baseline biopsy.

*Mean fiber area *and *fiber type distribution *will be analyzed as described by Andersen & Aaagaard [5]. Serial sections (10 μm) of the muscle biopsy samples will be cut in a cryostat (-20°C), and routine ATPase histochemistry analysis will be performed after preincubation at pH 4.37, 4.60, and 10.30.

*Number and activation status of satellite cells *in muscle biopsies will be assessed by immunohistochemistry, as previously described by Mackey et al. [8]. The primary antibodies for Pax7, Type I myosin (A4.951), and laminin will be applied to the same section. In this approach, sites of Pax7 antigenicity are visible by light microscopy while fluorescence microscopy on the same section reveals which fibres are type I and type II. The same sections can be used to determine the number of myonuclei associated with type I and type II fibres. Active satellite cells can be distinguished from quiescent with the aid of double staining for satellite cells and Ki67, as described [9].

*Levels of Intracellular Signaling Molecules*: Gene expression of different signalling molecules involved in hypertrophy and atrophy, i.e. Insulin-like Growth Factor 1 (IGF-1) and Atrogin-1, will be measured by real-time Reverse Transcription Polymerase Chain Reaction (RT-PCR), as previously analyzed by our laboratory [10,11].

#### Secondary outcome

Physical function tests will include maximum isometric quadriceps muscle strength test by maximum voluntary contraction (MVC)-measurements using '*Good Strength'-*chair, and maximum muscle power will be assessed by Leg Extensor Power (LEP)-measurements in Nottingham Power-Rig.

*Maximum voluntary contraction*: The participants will be fixated in the Good Strength chair (Metitur Oy, FI-40250 Jyväskylä, Finland. CE certificate: NB ID 0537) with a fixed knee angle of 60 degrees (0 degree = full extension) [12]. Maximum isometric muscle torque will be assessed for both quadriceps (extension) and hamstring (flexion) for both legs. Which leg will be tested first will be randomly selected. A minimum of 3 attempts will be carried out for each leg, and the participants will continue until one attempt is lower than the maximum. The overall maximum attempt (for both legs) will be used as test result.

*Leg Extensor Power*: The participant is seated in the Power Rig (Nottingham Power Rig, Queen's Medical Centre Nottingham, NG7 2UH, United Kingdom) with joint angles as if the participant was rising from a chair. The participants extend one leg as forcefully as possible, and the velocity of the flywheel is measured by an optoswitch and used to calculated the average leg extensor power in the push [13]. Each leg is tested separately, a minimum of 5 attempts is carried out for each leg, however the participant continues until two attempts are lower than the maximum. The overall maximum attempt for both legs is used as the test result.

*Systemic inflammation, lipid and glucose metabolism *will be measured in fasting blood samples. The participants will arrive at the hospital after an overnight fast (minimum 8 hours) and have a 10 ml venous blood sample drawn according to standard clinical guidelines.

Circulating cytokines will be analyzed in plasma using ethylenediaminetetraacetate (EDTA) as an anticoagulant. Plasma is stored at - 80 C until analysis. C-reactive Protein (CRP), Tumor Necrosis Factor alpha (TNF-α), Interleukin-6 (IL-6), Interleukin-18 (IL-18), Interleukin-4 (IL-4) and Interleukin-10 (IL-10) are determined by enzyme-linked immunosorbent assay (ELISA) kits, as previously described by Lindegaard et al [14].

Total cholesterol (TCHO), high density lipoprotein (HDL)-cholesterol, low density lipoprotein (LDL)-cholesterol, triglycerides, glucose and Insulin are measured using standard laboratory procedures.

*Whole Body composition *will be assessed by whole body Dual-Energy X-ray Absorptiometry, (DXA scan) (DPX-IQ Lunar, Lunar Corporation Madison, WI, USA). Transverse scans at 1 cm intervals are made from head to toe measuring the absorption of x-ray beams at two different energy levels as these are sent through the body. Since the different chemical compounds (bone, fat, and fat-free/bone-free mass) in the body absorb the intensity of the X-rays differently, the scan allows for a valid determination of bone mass, fat mass and fat-free/bone-free mass [15].

The DXA scans will be carried out in the morning after an overnight fast. The participants will be asked to standardize their food and water intake on the day prior to scanning to minimize difference in overall hydration as well as extra- and intracellular water distribution as much as possible [16].

*Patient reported outcomes related to Health Related Quality of Life (QoL) *will be assessed be standardized questionnaires: European Organization for Research and Treatment of Cancer Quality of Life Questionnaire (EORTC QLQ-C30) [17] and Medical Outcomes Study Short Form (MOS SF-36) [18]. EORTC QLQ-C30 comprises five functional scales, nine symptom scales or items, and a global health status/quality of life scale. A high score on the functional and global health status/quality of life scale represents a high or healthy level of functioning and high quality of life, while a high score for a symptom scale represents a high level of symptom burden. MOS SF-36 contains eight scales evaluating general health concepts and two summary scales: physical component scale and mental component scale.

### Sample size

Sample size is chosen to ensure significant muscular hypertrophy, evaluated by mean fiber area, in CON, among whom a 15% increase is estimated according to earlier studies.

N > (1,28*√(0.15*0.85))^2^/(0.15^2^) = 9,28. A minimum of 10 is required in each group, but due to clinical experience concerning possible drop out due to medical reasons 15 are included in each group.

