## Background

Testicular cancer (TC) is the most common form of cancer among young men in western countries [1], and remains the most curable solid tumor with a 10 year survival of 90 to 95% [2]. The standard treatment for patients with advanced germ cell cancer is 3 or 4 cycles of chemotherapy with cisplatin, etoposide and bleomycin (BEP) depending on prognostic factors. The treatment is highly effective, but the majority of patients experience severe adverse effects during treatment, and are at risk of developing considerable long-term morbidity, including second malignant neoplasms, cardiovascular disease, neurotoxicity, nephrotoxicity, pulmonary toxicity, hypogonadism, decreased fertility, and psychosocial problems [3]. In a study by Orre et al. the prevalence of chronic cancer related fatigue was 17.1% among TC patients compared to 9.7% in the general population. Regression analyses showed that poor quality of life (QoL), various psychosocial and somatic problems, and neuroticism were highly associated with presence of chronic cancer related fatigue [4].

Impaired muscular function and significant muscular fatigue are common complaints among TC patients undergoing chemotherapy. The cause of this muscular deconditioning is unknown, and knowledge regarding the effect of antineoplastic drugs on muscle function and morphology is very limited. There is also a lack of knowledge regarding whether TC patients will benefit from exercise training during chemotherapy.

The primary aim of the study is to investigate the effects of BEP-treatment on skeletal muscle, and to examine whether the treatment-induced muscular deterioration can be attenuated or even reversed by high intensity progressive resistance training (HIPRT) initiated on day 1 of the course of antineoplastic treatment. We have chosen a type of resistance exercise program that has proven to induce significant muscular hypertrophy in both healthy and diseased subjects [5]. Furthermore, the long term effect of an exercise rehabilitation program after the course of treatment will be investigated.

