### Analytic Plan

1-way repeated measures Analysis Of Variance (RM-ANOVA) will be used to evaluate test-data within groups for assessments at baseline, 9 and 21 weeks. 2-way ANOVA (group × time) will be used to test the effect of HIPRT for TC patients (STR vs. UNT), and BEP-treatment for training response (STR vs. CON) respectively. The equivalent non-parametric tests will be used for mRNA expression and protein levels. Significance level of 0.05 is chosen.

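### The sample size rests on within-group hypertrophy in the non-randomised healthy controls, so the stated minimum per group is not supported for the randomised STR vs UNT comparison

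*Protocol article*

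**What the plan says.** All references are to the protocol article.

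- **Sample size** names one objective: "Sample size is chosen to ensure significant muscular hypertrophy, evaluated by mean fiber area, in CON, among whom a 15% increase is estimated". The formula is "N > (1,28*√(0.15*0.85))^2^/(0.15^2^) = 9,28". The text continues "A minimum of 10 is required in each group", and the step to the final number is put down to "possible drop out due to medical reasons 15 are included in each group".
- **Randomization** allocates 15 patients to STR and 15 to UNT. The 15 CON subjects are assigned to training without randomisation.
- **Healthy control subjects** gives CON the role of showing the training response in young men who receive no chemotherapy.
- **Background** states a two-part primary aim: the effect of BEP on skeletal muscle, and "to examine whether the treatment-induced muscular deterioration can be attenuated or even reversed by high intensity progressive resistance training (HIPRT").
- **Analytic Plan** says that a group-by-time ANOVA "will be used to test the effect of HIPRT for TC patients (STR vs. UNT"), and also STR vs CON. It adds: "Significance level of 0.05 is chosen".

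The article gives no STR-UNT difference, no SD of fiber area or of its change, and no power for any comparison.

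**The concern.** The sizing target is a before-after change in one group of healthy men. The randomised question is a difference between two independent groups of patients. A requirement worked out for the first does not carry over to the second, for two reasons.

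- **Variance.** At equal SD and equal n, the difference between two independent mean changes has twice the variance of one mean change. The printed formula has no between-group term.
- **Effect.** The 15% is a training gain without chemotherapy. The STR-UNT difference depends on how far UNT deteriorates and how far training still works in STR under BEP. The article's Discussion itself raises hypogonadism as a possible cause of a weaker response.

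The increase from 10 to 15 does not close the gap, because it is attributed wholly to dropout.

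A reader who takes the section at face value will think the patient arms were sized for the randomised comparison. CON could then respond exactly as planned while the precision of STR vs UNT remained unknown.

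**Working it through.** **1. The plan's own figure.** Inputs from Sample size: z = 1.28, p = d = 0.15.

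N > z² × p(1 − p) / d² = 1.6384 × 0.1275 / 0.0225 = 9.284

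This reproduces the printed 9.28, which rounds up to 10. Recruiting 15 to keep 10 allows a loss of 1 − 10/15 = 33%. The arithmetic is right. It is a one-sample calculation.

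**2. What the formula contains.** The term 0.15 × 0.85 is the variance of a proportion, used here for a percentage change in a continuous measure. Its implied SD is √0.1275 = 0.357, or 35.7%. The single z of 1.28 corresponds to one-sided 0.10 (two-sided 0.20), or to 90% power, but it is not labelled as either. It does not match the 0.05 level in the Analytic Plan, and alpha and power have no separate terms. With the same variance term and two-sided 0.05:

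- 80% power: (1.96 + 0.8416)² × 0.1275 / 0.0225 = 44.5
- 90% power: (1.96 + 1.2816)² × 0.1275 / 0.0225 = 59.5

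At SD 35.7%, a paired t-test of a 15% change has about 22% power at n = 10 and 33% at n = 15.

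**3. What the chosen n can detect.** Noncentral t, two-sided 0.05, 80% power, d in units of the SD of change.

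- Between arms: df = 2n − 2, noncentrality d√(n/2)
- Within CON: df = n − 1, noncentrality d√n

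| Evaluable per group | STR vs UNT | Within CON |
|---|---|---|
| 10 | 1.32 SD | 1.00 SD |
| 15 | 1.06 SD | 0.78 SD |

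The normal approximation for the two-arm case, (1.96 + 0.8416) × √(2/n), gives 1.25 and 1.02. For 90% power the t-based values are 1.53 and 1.23.

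**4. Range in percentage points.** Both the 15-point STR-UNT difference and the SD of change are assumptions. The last column is the normal approximation 2 × (1.96 + 0.8416)² × (SD/15)², rounded up.

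| Assumed SD of change | Power, n = 10 | Power, n = 15 | n per arm for 80% |
|---|---|---|---|
| 10% | 89% | 98% | 7 |
| 15% | 56% | 75% | 16 |
| 20% | 36% | 51% | 28 |
| 25% | 25% | 35% | 44 |

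If the difference were half as large (7.5 points), power at SD 10% would be 36% at n = 10 and 51% at n = 15.

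**5. The two tests side by side.** With a 15-point effect and an assumed SD of 15%, the within-CON test has 80% power at n = 10 and 95% at n = 15. The STR vs UNT test has 56% and 75%.

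**The case against.** The strongest reply is that nothing here shows 15 per arm to be too few. The documents give neither an SD of change nor an STR-UNT difference. At SD 10% and a full 15-point difference, even 10 per arm has 89% power. The 15% gain in healthy men is also not a natural yardstick for STR vs UNT: the authors expect muscle loss during BEP, so loss in UNT would widen the difference, while a weaker training response in STR would narrow it. All of this stands. A reader might infer from the detectable differences that the trial is underpowered, or could not see a realistic effect. The documents do not support that.

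A second reply is that STR vs UNT is not the whole aim. The effect of BEP on muscle comes first in the Background, and the Discussion calls the muscular side effects of BEP the main aim. That also stands, but STR vs UNT remains part of the primary aim and the only comparison protected by randomisation.

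A third reply is that sizing detail may sit in a full protocol or analysis plan that is not shown. This does not help. The article does not defer the matter: it states the basis, prints the formula and declares the result a requirement for every group.

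Finally, a reader might conclude that CON, at least, is properly sized and that its calculation can stay. Step 2 of the working shows otherwise.

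**Conclusion.** The point holds in limited form. The stated basis, a within-group change in non-randomised healthy men, does not address STR vs UNT, so the minimum of 10 is not supported for the patient arms. The detectable STR-UNT difference is 1.32 SD of change at 10 evaluable per arm and 1.06 SD at 15. This assumes equal SDs in the arms, two-sided 0.05, 80% power and a t-based comparison of 9-week changes. The article does not state sidedness or power, so those two are conventions adopted here.

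Whether that is adequate cannot be settled from the documents: power for an assumed 15-point difference with 15 per arm runs from 98% to 35% over SDs of 10% to 25%. The point should be fixed, but it is a defect in the stated justification and does not call for a change in n, arms or analysis.

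**What to change.** Leave n unchanged and revise the Sample size section:

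1. Replace the statement that 10 are needed in every group with the detectable 9-week STR-UNT difference in change in mean fiber area, at 80% power and two-sided 0.05: 1.32 SD of change at 10 evaluable per arm and 1.06 SD at 15. Nine weeks is the right point because UNT are offered the training programme afterwards.
2. If percentage figures are given, label both the 15-point difference and the SD as assumptions and show the whole range from SD 10% to 25%, not one favourable or unfavourable value.
3. Do not keep the printed CON formula as it stands. Confine any CON calculation to the CON within-group test, and redo it with an SD of change and separate terms for alpha (0.05) and power.
4. Advisable but secondary: say that STR vs UNT will be reported as an estimate with a 95% CI.

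The cost is wording and a short recalculation, with no extra patients. The price is that the stated capability looks less favourable than it does now.

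### The minimum of 10 per group comes from a precision formula for a proportion with one unlabelled z value, although the outcome is a continuous mean; the number is not validly derived

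*Protocol article*

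**What the plan says.** The Sample size section of the protocol article names the target: "Sample size is chosen to ensure significant muscular hypertrophy, evaluated by mean fiber area, in CON". The assumed effect follows: "among whom a 15% increase is estimated according to earlier studies". The calculation and its conclusion, which extends to all arms, read "1,28*√(0.15*0.85))^2^/(0.15^2^) = 9,28. A minimum of 10 is required in each group". The number is then raised to 15 per group to allow for drop-out on medical grounds.

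The section does not say what 1.28 stands for, and no SD appears in the calculation.

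The Analytic Plan treats the outcomes as continuous. Within groups, "1-way repeated measures Analysis Of Variance (RM-ANOVA) will be used to evaluate test-data within groups" at baseline, 9 and 21 weeks. Between groups, a two-way ANOVA (group by time) compares STR with UNT and STR with CON. The level is fixed: "Significance level of 0.05 is chosen". Whether it is one- or two-sided is not stated.

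**The concern.** The printed expression has the form z² p(1 − p) / d², with p = d = 0.15. That gives the number of subjects needed to estimate a proportion of 15% to within 15 percentage points. In this plan the 15% is a relative rise in the mean of a continuous measurement. For such a quantity 0.85 has no meaning as one minus p, and the product 0.15 × 0.85 says nothing about how much fiber-area change varies between men. The power of a paired test or an ANOVA depends on that variation.

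A calculation meant to secure a significant result also needs one term for alpha and one for power. Only one z value is present.

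This paragraph is the article's only justification for the size of the trial, and mean fiber area is among the primary outcomes. The figure of 10 also acts as a floor: it implies that losing 5 of 15 (33%) in any group would be acceptable. It is applied to every group, including the two randomized arms, although the 15% was assumed only for the non-randomized controls.

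**Working it through.** **1. The plan's own figure.** Inputs from the Sample size section: z = 1.28, p = 0.15, d = 0.15.

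1.28² × 0.15 × 0.85 / 0.15² = 1.6384 × 0.1275 / 0.0225 = 9.28, rounded up to 10. The figure reproduces.

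**2. What 1.28 can be.** The upper tail of the standard normal beyond 1.28 is 0.100. There are two readings:

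- An alpha quantile: one-sided 0.10 or two-sided 0.20. Neither matches the 0.05 in the Analytic Plan, and there is then no power term.
- A power quantile for 90% power. The alpha term is then missing.

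The document does not say which is meant. Under either reading, one of the two required terms is absent.

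**3. Whether any alpha-0.05 version of the formula returns 10.** With everything else unchanged:

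- z = 1.645 (one-sided 0.05, no power term): 15.3
- z = 1.96 (two-sided 0.05, no power term): 21.8
- z = 1.96 + 0.842 (two-sided 0.05, 80% power): 44.5

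None does. These values are not required sample sizes, because the formula does not apply to this outcome. They show only that the printed 10 is not tied to the stated 0.05.

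**4. What a calculation for a continuous change looks like.** The documents give no SD of the fiber-area change and no target power, so the SDs below are assumptions. The others are two-sided alpha 0.05 and a 15% mean change between two time points. This is simpler than the planned ANOVA over three time points.

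Within one group, paired t-test: noncentrality = (0.15 / SD) × √n, with n − 1 degrees of freedom. Example: for SD 0.15 and n = 10, noncentrality = 1.0 × √10 = 3.16 and power = 80%.

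Between two arms, t-test on the difference in change: noncentrality = (0.15 / SD) × √(n/2), with 2n − 2 degrees of freedom. The 15% between-arm difference is a further assumption, because the article gives no effect size for STR against UNT.

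| Assumed SD of change | n for 80% power, paired | Paired power, n = 10 | Paired power, n = 15 | Between-arm power, 10 per arm | Between-arm power, 15 per arm |
|---|---|---|---|---|---|
| 10% | 6 | 99% | >99% | 89% | 98% |
| 15% | 10 | 80% | 95% | 56% | 75% |
| 20% | 16 | 56% | 77% | 36% | 51% |
| 25% | 24 | 40% | 58% | 25% | 35% |

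The answer depends on the SD, the one input that the printed formula does not contain.

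**The case against.** The strongest defence is that the sizes may be adequate even though the derivation is wrong. Ten men give 80% power for a paired 15% change if the SD is about 15%, and 99% if it is 10%. Fifteen men keep 80% power up to an SD of about 19%. The article is also condensed: the SD may stand in the full protocol or in the earlier studies it relies on, so its absence from the page is not in itself a fault. All of this stands. It limits the point to the calculation that is printed, but does not rescue that calculation, because a stated formula is not something left to another document.

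A reader might go further in three ways that the documents do not support:

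- **That the trial is too small**, needing 22 or 45 per group (step 3 rounded up). Those numbers come from changing z in a formula that does not apply. The same holds for any power obtained by treating √(0.15 × 0.85) = 0.357 as the SD of fiber-area change.
- **That 1.28 plainly contradicts the 0.05 level.** This follows only if 1.28 is an alpha quantile. As a 90% power quantile it contradicts nothing; the alpha term is simply missing.
- **That the calculation amounts to 50% power.** This too depends on the alpha reading.

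**Conclusion.** The point holds as an error of method; the arithmetic itself is correct. A precision formula for a proportion was applied to a continuous mean, with one unlabelled z value where alpha and power each need a term. The minimum of 10 per group therefore has no valid derivation, nor does the implied allowance for falling from 15 to 10.

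Whether 10 or 15 is enough cannot be settled from the article. Over assumed SDs of 10 to 25%, 80% power for the change within the controls needs between 6 and 24 men. For the randomized comparison, under a further assumed 15% difference in change, power at 15 per arm lies between 98% and 35%. These ranges rest on two-sided 0.05 and a comparison of two time points, and they illustrate how sensitive the answer is. They are not a finding that the trial is underpowered.

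**What to change.** Delete the proportion formula and the sentence that 10 are required. Replace them with a calculation for a continuous change at two-sided 0.05, using the SD of fiber-area change from the same earlier studies that supplied the 15%, and label the alpha and power terms.

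Keep 15 per group. State the power with 15 enrolled and with 10 evaluable, over a range of SDs that starts no higher than 10%, for two quantities:

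- the change within the controls, which is the stated sizing target;
- the difference in change between STR and UNT, with its own assumed effect. The minimum is applied to each group, and this is the randomized comparison.

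The cost is one rewritten paragraph and no additional patients. The stated justification may become less favourable, particularly for the randomized comparison.
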